## 8.2 Reporting Procedure

### 8.2.1 Site

#### 8.2.1.1 Adverse Events

AEs should be reported on an AE Form (and where applicable on an SAE Form). AEs should be completed at each visit and the information recorded on the case report form (eRDC) / or paper form as appropriate.

AEs will be reviewed using the Common Terminology Criteria for Adverse Events (CTCAE), version 4.0 (see Appendix 4). Any AEs experienced by the patient but not included in the CTCAE should be graded by an Investigator and recorded on the AE Form in accordance with the following guidelines: Grade (1) Mild, Grade (2) Moderate, Grade (3) Severe, Grade (4) Life-threatening or Grade (5) Death. For each sign/symptom, the highest grade observed since the last visit should be recorded.

#### 8.2.1.2 Serious Adverse Events

For more detailed instructions on SAE reporting refer to the SAE Form Completion Guidelines contained in the Investigator Site File (ISF).

AEs defined as serious and which require reporting as an SAE should be reported on an SAE Form. When completing the form, the Investigator will be asked to define the causality and the severity of the AE which should be documented using the CTCAE version 4.0.

On becoming aware that a patient has experienced an SAE, the Investigator (or delegate) must complete, date and sign an SAE Form. The form should be scanned to the Trials Office email address listed below as soon as possible and no later than 24 hours after first becoming aware of the event:

**To report an SAE by email, email a scanned copy of the SAE form to:**

[[contact]](mailto:[contact]) (cc in trial mailbox: [[contact]](mailto:[contact]))

On receipt the ALS Trials Office will allocate each SAE a unique reference number. This number will be included in a response e-mail as acknowledgement of receipt. If confirmation of receipt is not received within 1 working day please contact the Trials Office. The SAE reference number should be quoted on all correspondence and follow-up reports regarding the SAE. The response e-mail from the ALS Trials Office should be filed with the SAE Form in the ISF.

For SAE Forms completed by someone other than the Investigator the Investigator will be required to countersign the original SAE Form to confirm agreement with the causality and severity assessments. The form should then be returned to the ALS Trials Office in the post and a copy kept in the ISF.

Investigators should also report SAEs to their own Trust in accordance with local practice.

#### 8.2.1.3 Provision of follow-up information

Patients should be followed up until resolution or stabilisation of the event. Follow-up information should be provided on a new SAE Form (refer to the SAE Form Completion Guidelines for further information).

---

## 8.2.2 Trials Office

On receipt of an SAE Form seriousness and causality will be determined independently by a Clinical Coordinator. An SAE judged by the Investigator or Clinical Coordinator to have a reasonable causal relationship with the trial medication will be regarded as a Serious Adverse Reaction (SAR). The Clinical Coordinator will also assess all SARs for expectedness. If the event meets the definition of a SAR that is unexpected (i.e. is not defined in the Investigator Brochure) it will be classified as a Suspected Unexpected Serious Adverse Reaction (SUSAR).

## 8.2.3 Reporting to the Competent Authority and Research Ethics Committee

### 8.2.3.1 Suspected Unexpected Serious Adverse Reactions

The ALS Trials Office will report a minimal data set of all individual events categorised as a fatal or life threatening SUSAR to the Medicines and Healthcare products Regulatory Agency (MHRA), Research Ethics Committee (REC) and to the Sponsor (University of Birmingham) within 7 days. Detailed follow-up information will be provided within an additional 8 days.

All other events categorised as SUSARs will be reported within 15 days.

### 8.2.3.2 Serious Adverse Reactions

The ALS Trials Office will report details of all SARs (including SUSARs) to the MHRA and REC annually from the date of the Clinical Trial Authorisation, in the form of a Developmental Safety Update Report (DSUR).

### 8.2.3.3 Adverse Events

Details of all AEs will be reported to the MHRA on request.

### 8.2.3.4 Other safety issues identified during the course of the trial

The MHRA and REC will be notified immediately if a significant safety issue is identified during the course of the trial.

## 8.2.4 Investigators

Details of all SUSARs and any other safety issue which arises during the course of the trial will be reported to Principal Investigators. A copy of any such correspondence should be filed in the ISF.

## 8.2.5 Data Monitoring Committee

The independent Data Monitoring Committee (DMC) will review all SAEs.

## 8.2.6 Manufacturer of Investigational Medicinal Product

All Serious Adverse Reactions (SARs) and Suspected Unexpected Serious Adverse Reaction (SUSARs) will be reported to the TikoMed Medical Expert by email or fax within 72 hours of the sponsor categorising the event as a SAR/SUSAR. Subsequent acknowledgement from TikoMed is expected within 48 hours of receipt.

## 9. DATA HANDLING AND RECORD KEEPING

### 9.1 Data Collection

Data will be collected during this clinical trial by utilising both electronic remote data capture (eRDC) systems and paper case report forms (CRF).

The Case Report Form (CRF) will comprise the following forms:

**Table 3 ALS Trial Case Report Form**

| Form                                             | Summary of data recorded                                                                                                                                                                                | Schedule for submission                | Paper/eRDC |
|--------------------------------------------------|---------------------------------------------------------------------------------------------------------------------------------------------------------------------------------------------------------|----------------------------------------|------------|
| Eligibility Form (checklist)                     | Confirmation of eligibility and satisfactory screening investigations where necessary                                                                                                                   | Faxed/emailed at point of registration | Paper      |
| Registration Form                                | Patient details and registration number                                                                                                                                                                 | Faxed/emailed at point of registration | Paper      |
| Treatment Extension Registration Form            | Patient details and registration number                                                                                                                                                                 | Faxed/emailed at point of re-consent   | Paper      |
| Screening Visit                                  | Visit details including confirmation of blood tests and vital signs, records of medical history (including abnormal blood tests/values) and concomitant medications                                     |                                        | eRDC       |
| Treatment Form                                   | Actual IMP dose, dates given, details and reasons for dose reductions and delays; details of supportive treatment, confirmation of blood tests, vital signs, records of AEs and concomitant medications | Within 1 week of treatment visit       | eRDC       |
| Treatment Form (Week 11 onwards – as applicable) | Actual IMP dose, dates given, details and reasons for dose reductions and delays; details of supportive treatment, confirmation of blood tests, vital signs, records of AEs and concomitant medications | Within 1 week of treatment visit       | eRDC       |

|                                                       |                                                                                                                                                                         |                                                                                      |                                                             |
|-------------------------------------------------------|-------------------------------------------------------------------------------------------------------------------------------------------------------------------------|--------------------------------------------------------------------------------------|-------------------------------------------------------------|
| Adverse Event Form                                    | AE start and stop dates, grade, outcome and causality assessed by clinician                                                                                             | Alongside each visit form                                                            | eRDC                                                        |
| Concomitant Medication Form                           | Concomitant medications start and stop dates, dose, route, frequency and indication                                                                                     | Alongside each visit form                                                            | eRDC                                                        |
| ALSFRS-R                                              | Patient response to ALSFRS                                                                                                                                              | Within 2 weeks of visit date                                                         | Paper initially and then transferred to eRDC by study team. |
| ALSAQ-40 Questionnaire                                | Patient response to ALSAQ-40                                                                                                                                            | Within 2 weeks of visit date                                                         | Paper initially and then transferred to eRDC by study team. |
| Biochemistry                                          | Date, visit, results, clinical significance                                                                                                                             | Within 2 weeks of visit date                                                         | eRDC                                                        |
| Haematology                                           | Date, visit, results, clinical significance                                                                                                                             | Within 2 weeks of visit date                                                         | eRDC                                                        |
| Pharmacokinetics                                      | Date, visit, sample collection, time taken                                                                                                                              | Within 2 weeks                                                                       | eRDC                                                        |
| Biomarker Sample                                      | Date, visit, sample collection, time taken                                                                                                                              | Within 2 weeks                                                                       | eRDC                                                        |
| Liver Specific Toxicity – additional information form | For the collection of additional information see Section 8.1.2.2 and Appendix 5 of the protocol                                                                         | Within 72 hours of liver toxicity event i.e elevated ALT, Bilirubin (see Appendix 5) | eRDC                                                        |
| Follow-up Form                                        | Date, visit details including clinical assessment and results of trial procedures                                                                                       | Within 2 weeks of final visit                                                        | eRDC                                                        |
| Single point Long-term Remote Follow Up Form          | Date, Re-consent, ALSFRS-R, ALSAQ-40, Concomitant Medication                                                                                                            | Quarter 1 2021                                                                       | eRDC                                                        |
| Unscheduled visit form                                | As required                                                                                                                                                             |                                                                                      | eRDC                                                        |
| End of treatment form                                 | Date and visit details including a Summary of protocol defined treatment and reasons for treatment discontinuation, clinical assessment and results of trial procedures | Within 2 weeks of visit date                                                         | eRDC                                                        |

|                 |                                                                       |                                                  |      |
|-----------------|-----------------------------------------------------------------------|--------------------------------------------------|------|
| Death Form      | Date and cause of death                                               | Immediately upon notification of patient's death | eRDC |
| Deviation Form  | Completed in the event of a deviation from the protocol               | Immediately upon discovering deviation           | eRDC |
| Withdrawal Form | Used to notify the Trials Office of patient withdrawal from the trial | Immediately upon patient withdrawal              | eRDC |

#### Ad hoc forms

Serious Adverse Event Form

Relapse/Death Report Form

Pregnancy Notification Form

## 9.2 Data Collection Procedure

### 9.2.1 Electronic Remote Data Capture (eRDC) systems only

The majority of patient clinical data will be collected via bespoke electronic data capture systems (eRDC) developed by the CRCTU programming team. Access to the eRDC system will be via standard web portals software (Microsoft Internet Explorer Version 8+, Firefox and/or Chrome) and individual site staff will be granted access to the system via unique username and password. Additional detailed information/training will be provided by the sponsor via 1:1 training throughout the study and an eRDC guidance/completion document will be provided to study site personnel.

### 9.2.2 Paper Case Report Forms only

The CRF must be completed, signed/dated and returned to the ALS Trials Office by the Investigator or an authorised member of the site research team (as delegated on the Site Signature and Delegation Log) within the timeframe listed above. *The exceptions to this are the SAE Form and Withdrawal Form which must be co-signed by the Investigator.*

Entries on the CRF should be made in ballpoint pen, in blue or black ink, and must be legible. Any errors should be crossed out with a single stroke, the correction inserted and the change initialled and dated. If it is not obvious why a change has been made, an explanation should be written next to the change.

Data reported on each form should be consistent with the source data or the discrepancies should be explained. If information is not known, this must be clearly indicated on the form. All missing and ambiguous data will be queried. All sections are to be completed before returning.

Data not captured in the source data for e.g. Quality of Life, this data will be recorded directly onto the CRF.

In all cases it remains the responsibility of the Investigator to ensure that the CRF has been completed correctly and that the data are accurate. The completed originals should be sent to the ALS Trials Office and a copy filed in the Investigator Site File.

---

Trial forms may be amended by the Trials Office, as appropriate, throughout the duration of the trial. Whilst this will not constitute a protocol amendment, new versions of the form must be implemented by participating sites immediately on receipt.

### 9.3 Archiving

It is the responsibility of the Principal Investigator to ensure all essential trial documentation and source records (e.g. signed Informed Consent Forms, Investigator Site Files, Pharmacy Files, patients' hospital notes, copies of CRFs etc) at their site are securely retained for at least 25 years after the end of the trial or following the processing of all biological material collected for research, whichever is the later. Do not destroy any documents without prior approval from the CRCTU Document Storage Manager.

## 10. QUALITY MANAGEMENT

### 10.1 Site Set-up and Initiation

All sites will be required to sign a *Clinical Study Site Agreement* prior to participation. In addition all participating Investigators will be asked to sign the necessary agreements and *Investigator registration forms* and supply a current CV to the ALS Trials Office. All members of the site research team will also be required to sign the *Site Signature and Delegation Log*, which should be returned to the ALS Trials Office. Prior to commencing recruitment all sites will undergo a process of initiation. Key members of the site research team will be required to attend either a meeting or a teleconference covering aspects of the trial design, protocol procedures, Adverse Event reporting, collection and reporting of data and record keeping. Sites will be provided with an Investigator Site File *and a Pharmacy File* containing essential documentation, instructions, and other documentation required for the conduct of the trial. The ALS Trials Office must be informed immediately of any change in the site research team.

### 10.2 On-site Monitoring

Monitoring will be carried out as required following a risk assessment and as documented in the *ALS Quality Management Plan*. Additional on-site monitoring visits may be triggered for example by poor CRF return, poor data quality, low SAE reporting rates, excessive number of patient withdrawals or deviations. If a monitoring visit is required the Trials Office will contact the site to arrange a date for the proposed visit and will provide the site with written confirmation. Investigators will allow the *ALS* trial staff access to source documents as requested.

### 10.3 Central Monitoring

Where a patient has given explicit consent sites are requested to send in copies of signed Informed Consent Forms for in-house review.

Trials staff will be in regular contact with the site research team to check on progress and address any queries that they may have. Trials staff will check incoming Case Report Forms for compliance with the protocol, data consistency, missing data and timing. Sites will be sent Data Clarification Forms requesting missing data or clarification of inconsistencies or discrepancies.

Sites may be suspended from further recruitment in the event of serious and persistent non-compliance with the protocol and/or GCP, and/or poor recruitment. Any major problems identified during monitoring may be reported to *the Trial Management Group*, and the relevant regulatory bodies. This includes reporting serious breaches of GCP and/or the trial protocol to the Research Ethics Committee (REC) and the Medicines for Healthcare products Regulatory Agency (MHRA).

### 10.4 Audit and Inspection

The Investigator will permit trial-related monitoring, audits, ethical review, and regulatory inspection(s) at their site, providing direct access to source data/documents.

Sites are also requested to notify the ALS Trials Office of any MHRA inspections.

### 10.5 Notification of Serious Breaches

In accordance with Regulation 29A of the Medicines for Human Use (Clinical Trials) Regulations 2004 and its amendments the Sponsor of the trial is responsible for notifying the licensing authority in writing of any serious breach of:

- The conditions and principles of GCP in connection with that trial or;
- The protocol relating to that trial, within 7 days of becoming aware of that breach

For the purposes of this regulation, a “serious breach” is a breach which is likely to effect to a significant degree:

- The safety or physical or mental integrity of the subjects of the trial; or
- The scientific value of the trial

Sites are therefore requested to notify the Trials Office of a suspected trial-related serious breach of GCP and/or the trial protocol. Where the Trials Office is investigating whether or not a serious breach has occurred sites are also requested to cooperate with the Trials Office in providing sufficient information to report the breach to the MHRA where required and in undertaking any corrective and/or preventive action.

## 11. END OF TRIAL DEFINITION

The end of trial will be the date of Last Patient Last Visit (LPLV). The Trials Office will notify the MHRA and the REC that the trial has ended and a summary of the clinical trial report will be provided within 12 months of the end of trial.

After closure of the trial with the MHRA the Sponsor is no longer required to notify the MHRA and main REC of changes of Principal Investigator. However, sites should continue to notify the Trials Office of changes in Principal Investigator by completing and returning (where required) an Investigator Registration Form together with a current signed and dated CV.

As a result of the ongoing COVID-19 pandemic, and the high at risk status of study participants, further recruitment and study treatment was paused temporarily. A decision was made by the funders and sponsor to terminate the study prematurely in October 2020. Last patient treatment visits were conducted in March 2020, however further follow up visits are planned to start in Quarter 1 of 2021. The last remote follow-up visit will be regarded as the last data capture for this trial.

## 12. STATISTICAL CONSIDERATIONS

### 12.1 Definition of Outcome Measures

Outcome measures are listed in Section 2.

### 12.2 Analysis of Outcome Measures

Numerical outcomes will be summarised and presented as means and standard deviations where the outcome is approximately normal; or median and inter-quartile ranges where non-normal.

#### 12.2.1 Analysis of Primary Outcome Measures

##### 12.2.1.1 Safety

The number of SAEs and AEs will be calculated and summarised. Furthermore, the number of patients experiencing each will be calculated. Each of these analyses will be broken down by grade, relatedness, event type (admitting event for SAEs); expectedness (SAEs only) and sequelae (SAEs only).

##### 12.2.1.2 Tolerability

Line listings for all intolerable adverse events will be given. The number of intolerable events will be calculated for each patient and summarised.

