### 2.3 Primary Outcome Measures

Our primary outcome measures will inform whether the therapy is feasible in this patient group.

- **Safety**
  - o Measured by the incidence of serious adverse events (SAEs) and adverse events (AEs) using CTCAE v4.0. Events will be summarised by grade, relatedness, admitting event (for SAEs); expectedness and sequelae.
- **Tolerability**
  - o Measured by the incidence of *intolerable adverse events*. An intolerable adverse event will satisfy all of the following criteria:
    1. Associated with a serious adverse event or a drug discontinuation of greater than three weeks;
    2. Grade 3, 4 or 5 in severity according to CTCAE version 4;
    3. In the opinion of the Investigator is i) definitely related or ii) probably related or iii) possibly related to the study drug treatment.
  - o Adverse events which are considered unrelated or probably not related will not be classed as intolerable events.
- **Quantity of study drug administered**
  - o Total drug administered, number of administrations, number and length of interruptions, and number of discontinuations will be reported.

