### 3. TRIAL DESIGN

This is a Phase IIa, pilot, single arm (uncontrolled) study, which seeks to recruit 15 patients with a diagnosis of ALS. The trial has no control arm because control outcomes will not address the primary objective of the trial. On recruitment to the study, patients will undergo a baseline screening assessment (within 14 days of initiation of treatment with ILB, or within 28 days for those patients discontinuing Riluzole at screening) to include a medical history, vital signs, haematology and blood biochemistry (laboratory assessments). Patients will also complete a baseline assessment on the ALS Functional Rating Scale (ALSFRS-R) and a Quality of Life Assessment (ALSAQ-40).

Patients will receive 2mg/kg of ILB subcutaneously, weekly for ten weeks (in the first instance), during out-patient visits at site. Dosing beyond 10 weeks (initially to 24 weeks and a maximum of up to 48 weeks) is dependent upon a formal review of the patient's eligibility, their wishes and the most suitable treatment options. If treatment extension is agreed (at the PIs discretion), patients will initially go on to complete an additional 14 weeks of treatment, with the option to extend treatment further. While patients are on the treatment extension phase of the trial a formal review will occur every 90 days.

During the clinical trial, regular assessments of adverse events, vital signs, haematology and blood biochemistry (laboratory assessments), ALSFRS-R and Quality of Life (ALSAQ-40) will be performed. These will be scheduled to occur weekly (during the main trial phase) and monthly thereafter in follow-up and/or treatment extension phase as per the schedule of events.

Following the suspension of treatment in March 2020 and the early termination of the study in October 2020 due to the COVID-19 pandemic, as well as the high risk status of participants, a single point long-term remote follow up visit will take place starting in Quarter 1 of 2021.

Patients will be asked to re-consent for this additional visit and data capture which will be conducted by the site PI via video call over an 8 week period.

During this remote visit, data collected will include ALSFRS-R, Quality of Life (ALSAQ-40) and concomitant medication – patients will be asked to provide information on any medication they have been taking for their condition, such as standard of care Riluzole.

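### Primary tolerability is named as an incidence, but Section 12.2.1.2 plans only listings and a summarised per-patient count; under the Section 12.2 default that count reads 0 (IQR 0–0) for 0 to 3 affected of 15

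*Protocol*

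**What the plan says.** Section 2.3 of the protocol, and the synopsis in the same terms, give tolerability as one of three primary outcomes: "Measured by the incidence of *intolerable adverse events*. An intolerable adverse event will satisfy all of the following criteria". The three criteria are an association with a serious adverse event or a drug discontinuation of more than three weeks, CTCAE Grade 3 to 5, and at least a possible relation to study drug.

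Section 12.2.1.2 is the only analysis text for this outcome. It has two sentences: "Line listings for all intolerable adverse events will be given", and "The number of intolerable events will be calculated for each patient and summarised".

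Section 12.2 gives the one general rule for numerical outcomes: they are "presented as means and standard deviations where the outcome is approximately normal; or median and inter-quartile ranges where non-normal".

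For safety, which Section 2.3 also describes as an incidence, Section 12.2.1.1 counts events and then adds: "Furthermore, the number of patients experiencing each will be calculated". Section 12.2.1.2 has no matching sentence.

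The planned size is 15 patients (Section 3), chosen on feasibility without a sample size calculation (Section 12.6). The synopsis makes a patient evaluable after at least one treatment, and Section 7.15 replaces patients who receive none.

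**The concern.** An incidence needs a numerator, a denominator and preferably an interval. Section 12.2.1.2 asks for none of these by name. It asks for a number per patient, and the only rule the protocol gives for summarising a number is mean (SD) or median (IQR). Neither suits a rare count in 15 patients: most values will be zero, so the median and quartiles sit at zero over a range of results that would be read quite differently if stated as incidences.

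Section 2.3 says that the primary outcomes inform whether the therapy is feasible in this population. With no control arm and no sample size calculation, an estimate with its uncertainty is the main thing the trial can offer on tolerability. The planned summary statistic may supply neither.

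**Working it through.** The protocol states no expected rate, threshold or precision for tolerability, so there is no figure of its own to reproduce. The check applies its summary rule to possible results.

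**Inputs**
- n = 15 (Section 3).
- Outcome per patient: number of intolerable events (Section 12.2.1.2).
- Rule: mean (SD) if approximately normal, otherwise median (IQR) (Section 12.2).
- k = number of patients with at least one intolerable event. This is an illustration, not a document figure; k = 0 to 5 was tried, with 1 or 3 events per affected patient.

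**Step 1: which branch of the rule applies.** With 12 zeros and 3 non-zero counts, a Shapiro–Wilk test gives p of about 3 × 10⁻⁶. The count is plainly non-normal, so the rule selects median (IQR).

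**Step 2: median and quartiles.** Sort the 15 counts; the first 15 − k are zero. The median is the 8th value. Under all nine standard quantile definitions and both hinge variants, the upper quartile lies at or between the 11th and 12th values.
- k ≤ 3: the 12th value is zero (15 − 3 = 12), so the result is 0 (IQR 0–0) under every definition, whether affected patients have 1 or 3 events each.
- k = 4: the 11th value is zero and the 12th is not. The upper quartile depends on the definition, from 0 to 1 with one event each.
- k = 5: the 11th value is non-zero, so the upper quartile is non-zero under every definition.

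**Step 3: what the same results look like as an incidence.** The estimate is k/15 with exact (Clopper–Pearson) 95% limits: the lower is the 2.5% point of Beta(k, 15 − k + 1), taken as 0 when k = 0, and the upper is the 97.5% point of Beta(k + 1, 15 − k).

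| Affected | Section 12.2 summary | Incidence | Exact 95% CI |
|---|---|---|---|
| 0/15 | 0 (0–0) | 0% | 0–21.8% |
| 1/15 | 0 (0–0) | 6.7% | 0.2–31.9% |
| 2/15 | 0 (0–0) | 13.3% | 1.7–40.5% |
| 3/15 | 0 (0–0) | 20.0% | 4.3–48.1% |

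**Step 4: how often this would arise.** With X ~ Binomial(15, p), P(1 ≤ X ≤ 3) = P(X ≤ 3) − P(X = 0). For an assumed p = 10% this is 74%; for an assumed p = 20% it is 61%. The protocol gives no p, so these are illustrations only.

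**Step 5: would the mean do better?** Three patients with one event each give a mean of 3/15 = 0.2 (SD 0.41). One patient with three events also gives 3/15 = 0.2 (SD 0.77). The mean does not identify the number of patients affected.

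**Step 6: smaller achieved sample.** Sections 1.2.4 and 11 report early termination, and the achieved n is not stated. The summary stays at 0 (0–0) under all nine quantile definitions for up to 2 affected of 11 to 14 patients, and up to 1 affected of 8 to 10.

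**The case against.** Four points stand against pressing this hard.

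First, a reader might infer that the planned tolerability output cannot distinguish no intolerance from a rate of 20%. The protocol does not support that. Section 12.2.1.2 requires a listing of every intolerable event and a count for each patient. With at most about 15 patients, anyone can count those affected, and the evaluable denominator is defined. This point stands in full.

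Second, the protocol uses the idea of summarising loosely. Section 2.3 applies it to tabulation by grade and relatedness, and Section 12.2.1.1 to trial-wide totals. Section 12.2.1.2 does not itself mention a median, so a frequency table would be a fair reading. This stands too, which is why the masking is conditional on applying the Section 12.2 default. That default is nevertheless the only rule given for numerical outcomes.

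Third, incidence is never defined as a proportion of patients, and a per-patient event count can express an event incidence. It would therefore go too far to call the two sections irreconcilable. The contrast with Section 12.2.1.1 remains: the same word is used for safety in Section 2.3, and there the patient count is written out.

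Fourth, the type of interval and the table layout are commonly left to the SAP, which is not at hand, and no decision rule turns on an interval. The absence of a confidence interval from the protocol is therefore no fault in itself. The components are also partly covered elsewhere: Section 12.2.1.1 counts patients with SAEs and AEs by grade and relatedness, and Section 12.2.1.3 covers interruptions and discontinuations. Those breakdowns need not be crossed, so they do not supply the composite count.

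One might also argue that the count is nearly binary because the stopping rules limit repeat events. That is only approximate: Sections 7.5 and 7.6 allow dosing to resume after some omitted doses. The result does not depend on it.

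**Conclusion.** The point holds as a mismatch between a primary outcome named as an incidence and an analysis paragraph that plans listings and a summarised count without the number of patients affected. Under the Section 12.2 default the summary is identical for observed incidences of 0% to 20.0% in 15 patients, with exact upper limits from 21.8% to 48.1%. In a smaller sample the masked range reaches 2 of 11 (18.2%) or 1 of 8 (12.5%).

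This rests on two assumptions: that the Section 12.2 rule is the one applied to the count, and that intolerable events are uncommon. It does not need one event per patient or a particular quartile definition. The failing is confined to the summary statistic; the events stay visible in the listings and no data are lost. It is a worthwhile and nearly free improvement to the reporting of a primary outcome, not a threat to the trial's conclusions.

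**What to change.** Amend Section 12.2.1.2 to read along these lines: *The number and proportion of evaluable patients (at least one treatment received) with at least one intolerable adverse event will be reported with an exact (Clopper–Pearson) 95% confidence interval. Line listings and the number of intolerable events per patient will be given as support; means and medians will not be used for this outcome.*

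The denominator follows the synopsis definition of an evaluable patient and adapts to whatever sample was achieved. The cost is one or two sentences. It needs no new data or assessment and changes no clinical rule.
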